### Outcome assessment

The effectiveness of both interventions will be evaluated at 3, 6, 9 and 12 months after inclusion in the study. The following outcomes will be investigated (Table 2):

**Table 2 Tab2:** Interventions and measurements in the follow-up after randomization

	Basal	3 months	6 months	9 months	12 months
Group allocation and intervention					
, Control group:					
Brief advice on smoking cessation	x	x	x	x	x
, Intervention group:					
Brief advice on smoking cessation + CO-oximetry	x	x	x	x	x
Outcome assessment					
Pattern of tobacco use (self-reported tobacco use)	x	x	x	x	x
Smoking cessation rates		x	x	x	x
Carbon monoxide (CO) levels in exhaled air by CO-oximetry in the intervention group	x	x	x	x	x
Carbon monoxide (CO) levels in exhaled air by CO-oximetry in the control group					x
Urinary cotinine tests	x	x	x	x	x
Nicotine dependence (Fagerström test scores)	x	x	x	x	x
Motivational stages of change (Prochaska and DiClemente’s stages)	x	x	x	x	x
Motivation for giving up smoking (Richmond test scores)	x	x	x	x	x

Smoking habit cessation, confirmed by a urinary cotinine test. The intervention will be considered effective if the test results are lower than 100 ng/mlSelf-declared abandonment of smoking habitReduction in the number of cigarettes smoked per day self-declared by the patientVariation in the motivational stage of change, according to the Prochaska and DiClemente’s Stages of Change model [33]Change in motivation to giving up smoking, according to the Richmond test [34]Change in nicotine dependence, measured according to the Fagerström test [35]

In the intervention group, the variation in CO levels in exhaled air, measured by CO-oximetry, will be registered. Main outcome will be mean urinary cotinine test differences between the two groups at 12 months. Secondary outcomes will include: urinary cotinine test results at 3, 6 and 9 months, CO-level differences at 12 months, as well as differences in self-reported tobacco use, nicotine dependence, Prochaska and DiClemente’s motivational stages of change and the Richmond test scores at 3, 6, 9 and 12 months of follow-up.

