A recent review [11] identified 12 studies in the period 1968–2009 reporting the effect of cigarette smoking on kidney allograft or recipient survival [14–25]. Although some of the revised studies showed contradictory results, in general cigarette smoking was associated with an increased risk of both graft loss and death. More recently, a large-scale study investigated the effect of smoking on post-kidney transplant outcomes in a retrospective cohort of 41,705 adult renal transplant recipients in the United States Renal Data System [26]. That work concluded that, compared with patients who have never smoked, new onset smoking after transplantation is associated with reduced allograft and patient survival. Similarly, a prospective study of 604 renal transplant recipients in The Netherlands showed that smoking after renal transplantation increases the risk of graft failure and mortality, while past smoking is a risk factor for mortality but not for graft failure [27]. Another European recent study in 402 randomly selected kidney graft recipients also concluded that smoking is a risk factor for kidney damage following renal transplantation [28].

Although there is evidence that active smoking plays an important role in allograft loss and patient mortality, this information has so far had little impact on patient management. Based on these results, smoking cessation should be promoted among patients undergoing kidney transplantation.

Both pharmacotherapy and non-pharmacological interventions could be used for the treatment of tobacco dependence. Non-pharmacological methods have the advantage of being inexpensive and feasible to implement, and may be particularly appropriate for transplant patients, who are usually polymedicated. The main non-pharmacological interventions for the treatment of tobacco dependence include advice from health professionals, self-help material, proactive telephone counseling, group or individual counseling, and intra-treatment or extra-treatment social support.

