
The results of the CO-oximetry in the intervention group will be collected at baseline, at 3 months, 6 months, 9 months and 12 months (visits 1–5). In the control group, CO-oximetry will only be performed at 12 months (visit 5).

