### Statistical analysis

Comparability of intervention and control groups will be checked in terms of the similarity of the distribution of the variables of interest at baseline. The response that patients rate, at different time points in the follow-up, will be compared in both arms of the study according to the outcomes studied.

The chi-square test or Fisher’s exact test will be used to compare proportions. Student’s *t* test will be used to compare means between groups with a normal distribution data. The Mann-Whitney test will be used to compare quantitative variables between groups in case of a non-normal distribution, determined by the Kolmogorov-Smirnov test.

Correlations between quantitative measurements will be determined by the Spearman’s rho correlation coefficient. Matched-pair data analysis will be also computed. Therefore, to evaluate the differences within each group at different time points, McNemar’s test and Wilcoxon’s signed ranks test will be calculated.

Additionally, clinical relevance from intervention will be studied by calculating the relative risk (RR), relative risk reduction (RRR), absolute risk reduction (ARR) and patient number needed to treat (NNT) at different times during the follow-up. All these measures will be presented with their confidence interval at 95 %.

A multivariate analysis using multiple linear regression and logistic regression will be performed, according to the considered response, to adjust the effectiveness of the intervention as potential confounders and to determine which other variables are associated with each of the results. Variables with statistical significance *p* <0.10 in the bivariate analysis will be selected to be included in the multivariate regression analysis. A modeling strategy of successive steps back will be used.

The degree of agreement between the self-declared smoking consumption, CO-oximetry results and the test results of urinary cotinine levels at 3, 6, 9 and 12 months after surgery will be evaluated. The agreement will be evaluated by the kappa index.

The validity of self-declared smoking consumption by patients regarding the results of the CO-oximetry and urinary cotinine test will be studied. Sensitivity, specificity and positive and negative predictive values will be determined, together with their 95 % confidence interval.

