Moreover, on the other hand this study will determine the correlation between self-reported exposure and cotinine findings using a urine test strip as well as those from CO-oximetry. Although CO measurement is not the best indicator of smoking cessation, at least for occasional smokers, due to its short half-life, the use of different outcome measures at different moments of time will allow us to see the consistency of the results among them.

Finally, if effectiveness of CO-oximetry is confirmed to reduce tobacco exposure in this subset of patients, we would have an intervention that is easy to use, economic and with considerable implications for cardiovascular risk prevention.

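### Cotinine-confirmed cessation and the mean-cotinine main outcome cannot tell nicotine from smoking apart from nicotine from replacement products, and the printed data items do not record such products specifically

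*Protocol article*

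**What the plan says.** Under Outcome assessment, the first listed outcome is "Smoking habit cessation, confirmed by a urinary cotinine test". The intervention counts as effective when the result is below 100 ng/ml, and no exception is given. The same section sets the primary comparison: "Main outcome will be mean urinary cotinine test differences between the two groups at 12 months". Self-declared abandonment is listed as a separate outcome, and "CO-level differences at 12 months" is a secondary one.

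The Background notes that "Both pharmacotherapy and non-pharmacological interventions could be used for the treatment of tobacco dependence", and goes on to favour non-drug methods for transplant patients, who already take many medicines. The Exclusion criteria do not mention nicotine products. The tobacco items under Independent measures, and Tables 1 and 2, do not list their use. The abstract's list of measurements includes entries for treatment and for drug use, but nothing ties either to nicotine products or to how an outcome is scored.

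Exhaled CO is read at all five visits in the intervention arm and only at 12 months in the control arm (Independent measures, Table 2). The Statistical analysis section compares self-report, CO and cotinine with one another: "The agreement will be evaluated by the kappa index". It also estimates the validity of self-report against both tests. CO does not enter the definition of confirmed cessation, and no ppm cut-off is printed.

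**The concern.** Cotinine is a breakdown product of nicotine, so it shows nicotine intake and not smoke. This is general pharmacology; the article does not state it. All patients receive advice to quit at five visits over 12 months, and nothing printed stops one of them from using a patch or gum. If that patient's cotinine is 100 ng/ml or more, three things follow:

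- The patient fails the confirmed-cessation rule despite having stopped smoking.
- The patient adds a high value to the arm's mean in the main outcome.
- In the validity analysis against cotinine, a truthful report of not smoking counts as a false one. Against CO it would be upheld.

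Unless product use is recorded, the analysis cannot identify these patients. The absolute risk reduction and NNT, which the plan uses to express clinical relevance, are the cessation measures most directly affected.

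**Working it through.** **Inputs from the document (Sample size).** Cessation after brief advice is 5–6 %. The increase considered relevant is 13 %, read here as percentage points, so the intervention rate is 18–19 %. There are 56 patients per arm with up to 10 % loss: 56 × 0.9 = 50.4, taken as 50 evaluable.

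**Assumptions.** f_c and f_i are the shares of true quitters in the control and intervention arms who use a nicotine product at month 12. Every such user is taken to test at or above 100 ng/ml. The document gives no figure for either share, so a range is shown.

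**Formulas.** With true rates p_c and p_i:

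- observed rates: p_c(1 − f_c) and p_i(1 − f_i)
- observed difference: p_i(1 − f_i) − p_c(1 − f_c) = 0.13 − p_i·f_i + p_c·f_c
- NNT = 1 / observed difference

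**Equal shares, true rates 5 % and 18 %:**

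| f in both arms | Observed rates | Difference | NNT | Risk ratio |
|---|---|---|---|---|
| 0 | 5.0 % and 18.0 % | 13.0 points | 7.7 | 3.6 |
| 10 % | 4.5 % and 16.2 % | 11.7 points | 8.5 | 3.6 |
| 20 % | 4.0 % and 14.4 % | 10.4 points | 9.6 | 3.6 |
| 30 % | 3.5 % and 12.6 % | 9.1 points | 11.0 | 3.6 |

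Starting from 6 % and 19 % gives the same differences and NNTs, because the difference is 13 × (1 − f). The factor (1 − f) cancels in the risk ratio, so that does not move.

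**Unequal shares, true rates 5 % and 18 %:**

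| f control | f intervention | Observed rates | Difference | Risk ratio |
|---|---|---|---|---|
| 0 | 20 % | 5.0 % and 14.4 % | 9.4 points | 2.9 |
| 10 % | 30 % | 4.5 % and 12.6 % | 8.1 points | 2.8 |
| 30 % | 10 % | 3.5 % and 16.2 % | 12.7 points | 4.6 |
| 20 % | 0 | 4.0 % and 18.0 % | 14.0 points | 4.5 |

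The absolute difference is inflated only if p_c·f_c > p_i·f_i, that is, if the control share exceeds 18/5 = 3.6 times the intervention share (19/6 = 3.2 times at the other end of the range). The risk ratio is inflated as soon as f_c > f_i.

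**In patients.** At 50 per arm, true quitters are 50 × 0.18 = 9 and 50 × 0.05 = 2.5. A 20 % share is 1.8 + 0.5 = 2.3 misclassified patients in the trial.

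**Power.** The plan's own figure is 80 %. A two-sided 5 % test with pooled variance, 50 per arm, gives 53 % at 5 % versus 18 % and 50 % at 6 % versus 19 %, so 80 % is not reproduced. That is a separate matter on which this point does not rest. With f = 20 % in both arms, the same calculation gives 44 % and 41 %, a loss of about 9 points.

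**Main outcome.** No size can be given for mean cotinine, because the document gives no cotinine mean or standard deviation and no level for product users.

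**The case against.** The strongest reply is that this is a condensed article. Rules on cessation aids, or a question about them, may stand in the full protocol or the case report form, and the abstract's entries for treatment and drug use leave room for that. This stands in part: a reader might infer that the trial does not record nicotine products at all, and the article cannot show that. It does print the outcome rule, its cut-off and an itemised data list, and the rule as printed makes no allowance.

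A reader might also infer that the trial judges cessation by cotinine alone. That holds only for the confirmed outcome. Self-declared abandonment counts the same patient as a quitter, and a patient with low CO and high cotinine would appear as discordant in the agreement analysis. Such discordance is not used to reclassify anyone.

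A third tempting reading is that the effect is necessarily biased towards none. More quit attempts in one arm do not imply a larger share of product users among its quitters, and the direction depends on shares that nobody has given. The Background's preference for non-drug methods suggests use may be low, and neither arm is supplied with a product.

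Finally, CO cannot be said to settle the question. The Discussion concedes: "Although CO measurement is not the best indicator of smoking cessation, at least for occasional smokers, due to its short half-life". There are further limits. Controls have no reading at 3, 6 and 9 months. Intervention patients have seen four earlier readings and may learn to abstain before the test. The exception would also be triggered by self-report, which the Discussion itself distrusts. Dropping product users from the mean-cotinine comparison would select on behaviour after randomisation and break the stated intention-to-treat analysis. These objections all stand, and they limit CO to a supporting, month-12 role.

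**Conclusion.** The point holds in limited form. The confirmed-cessation rule and the mean-cotinine main outcome do not separate nicotine from smoking from nicotine from replacement products, and the printed exclusions and data items neither bar nor specifically record such products. A true quitter on a product who tests at or above 100 ng/ml is misclassified on the confirmed outcome.

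The size rests wholly on assumed usage shares. Equal use of 10–30 % would shrink the 13.0-point difference to 11.7–9.1 points and leave the risk ratio unchanged; unequal use can move the result either way. The number of patients affected is probably small, about two at a 20 % share, but each arm is expected to yield few quitters. This is a cheap improvement and does not invalidate the trial.

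**What to change.** 1. Add one question on use of any nicotine product to the tobacco questions already asked at each visit.
2. At month 12 only, prespecify a sensitivity analysis of cessation in which self-reported non-smokers who use a nicotine product are classified by the exhaled CO already measured in both arms, with a ppm cut-off fixed before unblinding. Cotinine below 100 ng/ml remains the rule for everyone else and for the main cessation result.
3. Keep the mean-cotinine comparison in all randomised patients, and report nicotine-product use by arm beside it.

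This concerns recording and analysis only; it does not address whether patients may use such products. The cost is one question per visit, a sentence or two in the analysis text, and no new test. The downside is that CO has a short half-life, so confirmation is less stringent for this subgroup, and controls have no CO reading before month 12, so the analysis cannot be extended to earlier visits. Recruitment was still under way when the article was submitted. Patients who had already completed visits would lack the item, and the number affected should be reported.

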## Abstract

**Background:**

The cardiovascular risk in renal transplant patients is increased in patients who continue to smoke after transplantation.

The aim of the study is to measure the effectiveness of exhaled carbon monoxide (CO) measurement plus brief advisory sessions, in comparison to brief advice, to reduce smoking exposure and smoking behavior in kidney transplant recipients who smoke. The effectiveness will be measured by: (1) abandonment of smoking, (2) increase in motivation to stop smoking, and (3) reduction in the number of cigarettes smoked per day.

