**Methods/design:**

Design: a randomized, controlled, open clinical trial with blinded evaluation.

Scope: A Coruña Hospital (Spain), reference to renal transplantation in the period 2012–2015.

Inclusion criteria: renal transplant patients who smoke in the precontemplation, contemplation or preparation stages according to the Prochaska and DiClemente’s Stages of Change model, and who give their consent to participate.

Exclusion criteria: smokers attempting to stop smoking, patients with terminal illness or mental disability that prevents them from participating.

Randomization: patients will be randomized to the control group (brief advisory session) or the intervention group (brief advisory session plus measuring exhaled CO). The sample target size is *n* = 112, with 56 patients in each group. Allowing for up to 10 % loss to follow-up, this would provide 80 % power to detect a 13 % difference in attempting to give up smoking outcomes at a two-tailed significance level of 5 %. Measurements: sociodemographic characteristics, cardiovascular risk factors, treatment, rejection episodes, infections, self-reported smoking habit, drug use, level of dependence (the Fagerström test), stage of change (Prochaska and DiClemente’s Stages of Change model), and motivation to giving up smoking (the Richmond test).

Response: the effectiveness will be evaluated every 3, 6, 9 and 12 months as: pattern of tobacco use (self-reported tobacco use), smoking cessation rates, carbon monoxide (CO) levels in exhaled air measured by CO-oximetry, urinary cotinine tests, nicotine dependence (Fagerström test), motivational stages of change (Prochaska and DiClemente’s stages) and motivation to stop smoking (the Richmond test).

Analysis: descriptive statistics and linear/logistic multiple regression models will be performed. Clinical relevance will be measured as relative risk reduction, absolute risk reduction and the number needed to treat.

Ethics: informed consent of the patients and Ethical Review Board was obtained (code 2011/061).

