### Sample size

Meta-analyses have shown that around 5–6 % of smokers stop after the brief advisory session from a physician [36]. A 13 % increase in the cessation rate for the brief advisory session plus CO-oximetry over the brief advisory session alone is considered clinically relevant. The sample target size is, therefore, 112 patients, with 56 patients in each group of the trial. Allowing for up to 10 % loss to follow-up, this would provide 80 % power to detect a 13 % difference in smoking cessation outcomes at a two-tailed significance level of 5 %.

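### The 80 % power statement belongs to smoking cessation, not to the declared main outcome (mean urinary cotinine at 12 months), which has no stated SD, target difference or measurement scale

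*Protocol article*

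**What the plan says.** The protocol article names one main outcome, under Outcome assessment: "Main outcome will be mean urinary cotinine test differences between the two groups at 12 months". Cotinine-confirmed cessation, with a threshold of 100 ng/ml, heads the outcome list in the same section but is not called the main outcome.

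The Sample size section works with a binary outcome. It takes the control rate from the literature ("Meta-analyses have shown that around 5–6 % of smokers stop after the brief advisory session from a physician") and sets the target as follows: "A 13 % increase in the cessation rate for the brief advisory session plus CO-oximetry over the brief advisory session alone is considered clinically relevant". From this it derives 112 patients, 56 per group, and claims 80 % "power to detect a 13 % difference in smoking cessation outcomes at a two-tailed significance level of 5" per cent, allowing for 10 % loss.

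The abstract gives the same number and power for a differently worded outcome: "power to detect a 13 % difference in attempting to give up smoking outcomes at a two-tailed significance level of 5" per cent.

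The Discussion says how cotinine is obtained: "cotinine findings using a urine test strip as well as those from CO-oximetry". It does not say whether the strip reads positive/negative, in grades or as a number. The Statistical analysis section plans kappa, sensitivity and specificity for cotinine, which are categorical uses, but it also speaks of cotinine levels.

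**The concern.** A sample size statement supports the primary comparison only if both concern the same quantity. Here one is a proportion and the other a mean. Nothing in the article links them: there is no cotinine mean, SD or difference worth detecting. The test that decides the trial therefore has no power calculation.

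The scale adds to the problem. A mean needs a numeric reading, whereas the strip and the cut-off suggest a categorical one, and the article does not settle which applies.

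The choice matters because a mean responds weakly to a modest rise in quitting. Most patients in both arms are expected to go on smoking, and the spread of their cotinine values dilutes the contribution of the extra quitters. A null result on mean cotinine could then be read as evidence against CO-oximetry when the comparison had little chance of showing the planned effect.

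**Working it through.** **Inputs from the article.** Control cessation 5–6 %; difference 13 percentage points (5 vs 18 % or 6 vs 19 %); 56 per arm; 10 % loss, so 56 × 0.9 ≈ 50 evaluable; two-sided 5 %; 80 % power.

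**Step 1: the plan's own figure, for cessation.** n per arm = [1.96·√(2p̄(1−p̄)) + 0.842·√(p₁(1−p₁)+p₂(1−p₂))]² / (p₂−p₁)².

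- 5 vs 18 %: p̄ = 0.115, the two roots are 0.4512 and 0.4417, and n = (0.884 + 0.372)² / 0.0169 ≈ 93.4, so 94 per arm. After loss: 94/0.9, so 105.
- 6 vs 19 %: the roots are 0.4677 and 0.4586, and n ≈ 100.4, so 101 per arm. After loss: 101/0.9, so 113.
- A one-sided test would still need 74 to 79 per arm before loss.

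Power for 5 vs 18 % is Φ[(0.13·√n − 1.96·0.4512)/0.4417], which gives 53 % at n = 50 and 58 % at n = 56. For 6 vs 19 % it is 50 % and 55 %. Exact enumeration gives:

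| Evaluable per arm | Chi-square | Fisher |
|---|---|---|
| 50 | 53–56 % | 38–40 % |
| 56 | 56–60 % | 44–47 % |

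The stated 80 % is not reproduced. Some variants give about 112 per arm (for example 101 × 1.1 = 111.1, rounded up), so a per-arm figure may have been used as the total. The article does not allow this to be confirmed.

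**Step 2: the same planning effect on mean cotinine.** The article gives no cotinine distribution, so this is a model. Assumptions: quitters have cotinine near zero; continuing smokers have mean μ and coefficient of variation CV in both arms; the intervention acts only through quitting; values are not transformed. Then:

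- difference in means = 0.13μ
- variance in an arm with quit rate p = (1−p)(CV·μ)² + p(1−p)μ²
- d = 0.13μ / √(average variance); power ≈ Φ(d·√(n/2) − 1.96)

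Example, CV 0.5, 5 vs 18 %: the variances are 0.2850μ² and 0.3526μ², SD = 0.565μ, d = 0.230. At n = 50, Φ(1.15 − 1.96) ≈ 21 %.

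| CV (assumed) | Power, 50 per arm | Power, 56 per arm | Evaluable per arm for 80 % |
|---|---|---|---|
| 0 (limiting case) | 52–55 % | 56–60 % | 91–98 |
| 0.3 | 33–34 % | 36–37 % | 165–171 |
| 0.5 | 21 % | 23 % | 297–301 |
| 0.75 | 13 % | 14 % | about 555 |
| 1.0 | 10 % | 10–11 % | about 912 |

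The row CV = 0, where all continuing smokers have the same value, is the ceiling, and it is below 80 %.

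A simulation with lognormal smokers, 5.5 vs 18.5 % quitting and 50 per arm agrees. For CV 0.5, 0.75 and 1.0 the t test has 20, 14 and 11 % power. Mann-Whitney has 19–20 % and a t test on log values 39–47 %.

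**Step 3: relaxing the quitting-only assumption.** If cotinine in the intervention arm's continuing smokers also falls, power at 50 per arm for CV 0.5, 0.75 and 1.0 becomes 51, 30 and 20 % for a 10 % fall; 82, 56 and 37 % for a 20 % fall; and 97, 81 and 59 % for a 30 % fall.

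**The case against.** The best defence is that mean cotinine is a deliberate choice. The trial aims to reduce exposure as well as to produce quitters, and it lists fewer cigarettes per day as an outcome. Step 3 shows that a fall of 20–30 % among continuing smokers could give the mean comparison adequate power for some CVs, and more than cessation has. A log-scale analysis also narrows the gap: its 39–47 % is at or above Fisher's 38–40 % for cessation. All of this stands, so no general claim that cotinine is the less sensitive outcome can be made. It does not rescue the sample size statement, because the article plans no such fall and bases its 112 patients on quitting alone.

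Baseline cotinine is collected and could be adjusted for. In the Step 2 model even perfect adjustment leaves residual variance p(1−p)(1+CV²)μ², never smaller than the CV = 0 value, so the ceiling holds.

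Three stronger readings are tempting and are not supported.

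- A reader might infer that a strip result cannot be averaged. The article never states the read-out, and it refers to levels and ng/ml.
- A reader might take a narrow low power range as the trial's own figure. It depends on an assumed CV, on untransformed values and on no change among continuing smokers.
- A reader might see several rival success criteria that leave the sponsor free to pick one. The abstract does list objectives such as "1) abandonment of smoking, (2) increase in motivation to stop smoking", but the Outcome assessment section names a single main outcome, and the 100 ng/ml sentence reads as the definition of confirmed cessation.

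**Conclusion.** The mismatch is plain from the text and needs no model: the primary is a mean, the sample size is for a proportion, and the 80 % does not transfer. The unstated strip read-out is a second, smaller conflict that the article must resolve.

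The size of the power loss is conditional. If the effect acts only through quitting, an untransformed mean comparison at 50 per arm has roughly 10 to 33 % power for CV 1.0 down to 0.3, with a ceiling of about 50–60 % at 50 to 56 per arm. That it falls short of 80 % is robust within this model; the exact range is not.

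The sample size is also too small for the outcome it was built on. Cessation has about 53–60 % power by chi-square and 38–47 % by Fisher at 50 to 56 per arm. Realigning the primary outcome without restating the power would leave the 80 % claim wrong.

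**What to change.** 1. Name one primary outcome: cessation at 12 months confirmed by urinary cotinine below 100 ng/ml, compared between arms as a risk difference with 95 % confidence interval.
2. Make cotinine level at 12 months secondary. State the strip's read-out and analyse on that scale: as categories if graded or positive/negative, as a concentration only if the assay is quantitative.
3. Use cessation in the abstract's power statement in place of attempts to give up.
4. Restate the power for 5–6 % vs 18–19 %: about 53–60 % by chi-square, or 38–47 % by Fisher, with 56 per arm and about 50 after loss. To keep 80 %, the pooled calculation needs 94–101 evaluable per arm, or 105–113 randomized per arm after 10 % loss.

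If mean cotinine is kept as primary instead, it needs a quantitative assay, a stated SD and target difference, and its own sample size.

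**Cost.** No new data are needed, since cotinine is already collected at every visit. The trial is open and was recruiting at submission, so the change should be a dated amendment made before outcomes are compared by arm. Reduction without quitting would no longer count toward the primary conclusion, and the stated power becomes less favourable.
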